## Summary of clinical trial

|                                |                                                                                                                                                                                                                                                                                                                                                                                                                                                                                                                                                                                                                                                                                                                                                                                                                                                                                                                                                                                                                                                                                                                                     |
|--------------------------------|-------------------------------------------------------------------------------------------------------------------------------------------------------------------------------------------------------------------------------------------------------------------------------------------------------------------------------------------------------------------------------------------------------------------------------------------------------------------------------------------------------------------------------------------------------------------------------------------------------------------------------------------------------------------------------------------------------------------------------------------------------------------------------------------------------------------------------------------------------------------------------------------------------------------------------------------------------------------------------------------------------------------------------------------------------------------------------------------------------------------------------------|
| Name                           | A Multi-center, open, RETrospective and prospective observational Study to investigate Clinical oUtcomes and Efficacy of left ventricular assist device for Korean patients with cardiogenic shock : RESCUE                                                                                                                                                                                                                                                                                                                                                                                                                                                                                                                                                                                                                                                                                                                                                                                                                                                                                                                         |
| Purpose                        | The purpose of this study is to investigate the treatment status and clinical outcomes of cardiogenic shock in Koreans, as well as identify factors that can improve prognosis through retrospective and prospective registration of patients with cardiogenic shock from multiple institutions in Korea. In addition, we aim to determine the current usage and treatment effects of IABP and ECMO for cardiogenic shock.                                                                                                                                                                                                                                                                                                                                                                                                                                                                                                                                                                                                                                                                                                          |

| Duration                       | IRB approval date ~ December 31, 2019 (registration period: IRB approval date ~ December 31, 2018).
Data collection period: January 1, 2014 ~ December 31, 2019 (6 years).                                                                                                                                                                                                                                                                                                                                                                                                                                                                                                                                                                                                                                                                                                                                                                                                                                                                                                                                                       |
| Design                         | Retrospective and prospective, open, multi-center, and observational registry study                                                                                                                                                                                                                                                                                                                                                                                                                                                                                                                                                                                                                                                                                                                                                                                                                                                                                                                                                                                                                                                 |
| Estimated enrollemt            | 1000 participants (competitive registration after registering 1,000 participants)

 
• The group with left ventricular assist device insertion: more than 400 participants
 
• The group without left ventricular assist device insertion: more than 600 participants
 
                                                                                                                                                                                                                                                                                                                                                                                                                                                                                                                                                                                                                                                                                                                                                                                                      |
| Inclusion & exclusion criteria | 
[Inclusion criteria ]
 
 
1. 19 years old or older
 
2-1). Systolic blood pressure is less than 90mmHg for more than 30 minutes despite the fluid therapy, or Use of pressure boosting agents is necessary.
 
2-2). Peripheral hypopnea (cold skin, urine less than 30 cc per hour, impaired consciousness, lactate <math>\geq 2.0</math> mmol / l) or a person with pulmonary edema.
 
3. Causes of cardiogenic shock include acute myocardial infarction (including in coronary intervention), cardiomyopathy, myocarditis, pulmonary embolism, refractory ventricular tachycardia, shock during coronary intervention.
 
4. In-hospital cardiac arrest as a result of the cause stated in 'inclusion criteria 3'.
 
5. Those voluntarily consenting to the medical records and the data necessary for the study during the entire study period.
 
 
[Exclusion criteria]
 
 
1. Other causes except for cardiogenic shock (low blood pressure, septic, obstructive shock)
 
 |

|                      |                                                                                                                                                                                                                                                                                                                                                                                                                                                                                                                                                                                                                                                                                                                                                    |
|----------------------|----------------------------------------------------------------------------------------------------------------------------------------------------------------------------------------------------------------------------------------------------------------------------------------------------------------------------------------------------------------------------------------------------------------------------------------------------------------------------------------------------------------------------------------------------------------------------------------------------------------------------------------------------------------------------------------------------------------------------------------------------|
|                      | 
 
2. Shock with cardiac arrest outside the hospital
 
3. People with allergic reactions to anticoagulants such as heparin
 
4. Those who refused active treatment
 
                                                                                                                                                                                                                                                                                                                                                                                                                                                                                                                    |
| Detailed description | 
 
1) The selection / exclusion criteria for persons with cardiogenic shock should be verified by medical records from January 1, 2014 before the approval date of each institution's clinical trial screening committee.
 
2) If a cardiogenic shock to the selection criteria is found in the emergency room, general ward, or intensive care unit of the participating institutions, enroll in this study and fill in the information according to the e-CRF.
 
3) After 1, 6 and 12 months, visit the hospital for examination and procedures. The person in charge of the examination or the delegate of the examiner may follow the person by telephone or an outpatient visit.
 
 |
| Outcome measures     | 
Primary Endpoint
 
In-hospital death
 
Secondary Endpoints
 
 
1. Death in 28 days
 
2. Death during follow-up
 
3. Death, myocardial infarction, stroke, re-admission due to heart failure during follow-up
 
4. Number of days of intensive care unit
 
5. Hospitalization days
 
6. Lactate 24 hour clearance
 
7. Successful removal of left ventricular assist device (IABP, ECMO)
 
                                                                                                                                                                                                                                     |

## Clinical trial flow chart

|                                                          | Visit 1
(admission) | Follow-up*        |                     |                     |
|----------------------------------------------------------|------------------------|-------------------|---------------------|---------------------|
|                                                          |                        | Visit 2
(1M)   | Visit 3
(6M)     | Visit 4
(12M)    |
|                                                          |                        | 4
Week
±1wk | 24
Week
±4wks | 48
Week
±4wks |
| Obtaining consent                                        | X          |                   |                     |                     |
| Inclusion/exclusion criteria                             | X                      |                   |                     |                     |
| Height and weight/vital signs                            | X                      |                   |                     |                     |
| Demographic information and risk factors/medical history | X          |                   |                     |                     |
| Medication history                                       | X                      |                   |                     |                     |
| Investigation of cardiovascular event                    | X                      | X                 | X                   | X                   |
| Coronary angiography                                     | X                      |                   |                     |                     |
| Lt. ventricular assist device insertion                  | X                      |                   |                     |                     |
| Complications related to the procedure       | X                      |                   |                     |                     |
| Echocardiography                                         | X                      |                   |                     |                     |
| General blood chemistry test                             | X          |                   | X       |                     |
| Lactate, ScVO 2                               | X          |                   |                     |                     |
| CPK, CK-MB, Troponin, NT-ProBNP                          | X                      |                   | X                   |                     |

1. There must be a signature from the patient or their legal guardian on the consent form. As this study is a retrospective and prospective registry study, data can be collected from patients who meet the selection criteria for either undergoing coronary angiography, insertion or non-insertion of a left ventricular assist device, after obtaining consent for access to medical records.
2. Age, sex, risk factors, medical history, clinical diagnosis, etc.
3. Investigate whether complications such as limb ischemia, stroke, sepsis, major bleeding events, vascular injury during insertion, and failure of left ventricular assist device insertion occurred.
4. CBC, Creatinine, Fasting glucose level, AST, ALT, T-bilirubin, LDH, Sodium
5. Lactate and ScVO2 are measured every 6 hours from the onset of shock, and then once a day until shock recovery.

\* Telephone (landline) interviews are also allowed for information gathering without the subjects having to visit the hospital.

**6. Purpose and background of clinical trial****6.1. Purpose**

The purpose of this study is to investigate the treatment status and clinical outcomes of cardiogenic shock in Koreans, as well as identify factors that can improve prognosis through retrospective and prospective registration of patients with cardiogenic shock from multiple institutions in Korea. In addition, we aim to determine the current usage and treatment effects of IABP and ECMO for cardiogenic shock.

## 6.2. Background

Cardiogenic shock usually occurs as a fatal complication of acute myocardial infarction, cardiomyopathy, myocarditis, and rarely, sepsis. In particular, shock occurs in 5-8% of cases of ST-segment elevation myocardial infarction, and despite the development of various treatment techniques such as coronary intervention and coronary artery bypass grafting, a very high mortality rate of about 40% is still reported [1]. Shock is a term that encompasses all clinical situations in which cellular respiration is not properly carried out due to inadequate oxygen supply to tissues. It was first described by a French surgeon in 1737, and much progress has been made in the treatment and research of shock through the two World Wars and the Korean and Vietnam Wars. Types of shock include hypovolemic shock, represented by excessive bleeding due to trauma or surgery, septic shock caused by decreased peripheral vascular resistance due to infection, obstructive shock caused by circulatory disorders such as pulmonary embolism and cardiac tamponade, and cardiogenic shock caused by decreased cardiac output due to loss of cardiac pump function. The prominent characteristic of cardiogenic shock is that while the early mortality rate is the highest, once the patient recovers from shock, they can maintain a good quality of life with a better prognosis compared to other shocks. Currently, most of the studies related to cardiogenic shock published in Korea have selected patients through the arbitrary criterion of Killip class IV in acute myocardial infarction registry, so it is difficult to accurately determine the frequency and treatment status, mortality rate, etc. of cardiogenic shock caused by causes other than myocardial infarction. Since the adequacy of appropriate early treatment within 24 hours after the occurrence of cardiogenic shock determines the prognosis, it is essential to evaluate the treatment status and appropriateness of cardiogenic shock in Korea through research at the present time. In addition, the initial treatment of cardiogenic shock is primarily fluid therapy, mechanical ventilation, and vasopressor therapy, but if these are ineffective, left ventricular assist devices such as intra-aortic balloon pumps (IABP) and extracorporeal membrane oxygenation (ECMO) can be used. However, there are still no large-scale systematic studies in Korea to determine their effects.

Recently, in a study conducted by Thiele et al., the superiority of IABP treatment was not demonstrated compared to standard treatment group in patients with cardiogenic shock accompanied by acute myocardial infarction for whom early coronary intervention was scheduled [2]. As a result, research on the effectiveness and safety of mechanical circulatory support devices that can more effectively assist left ventricular function in cardiogenic shock is being actively pursued worldwide [3-6]. In particular, the expected benefits of ECMO, a left ventricular assist device that can be operated anywhere in emergency situations, are significant, and interest in ECMO procedures is rapidly increasing in Korea, with the number of procedures increasing rapidly. Therefore, it is urgent to evaluate the appropriateness and effectiveness of ECMO and conduct research on its effects.

## **7. Medical device information**

- ECMO: The Capiox Emergency Bypass System (Terumo, Tokyo, Japan) or Prolonged Life Support System (Maquet Cardiopulmonary AG, Hirrlingen, Germany)
- IABP (Datascope or Arrow)

## **8. Target disease**

Cardiogenic shock

## **9. Inclusion criteria, exclusion criteria, and targeted sample size and their basis**

### **9.1. Inclusion criteria**

1. 19 years old or older
- 2-1). Systolic blood pressure is less than 90mmHg for more than 30 minutes despite the fluid therapy, or Use of pressure boosting agents is necessary.
- 2-2). Peripheral hypoxia (cold skin, urine less than 30 cc per hour, impaired consciousness, lactate  $\geq 2.0$  mmol / l) or a person with pulmonary edema.
3. Causes of cardiogenic shock include acute myocardial infarction (including in coronary intervention), cardiomyopathy, myocarditis, pulmonary embolism, refractory ventricular tachycardia, shock during coronary intervention.
4. In-hospital cardiac arrest as a result of the cause stated in 'inclusion criteria 3'.
5. Those voluntarily consenting to the medical records and the data necessary for the study during the entire study period.

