## **11. Clinical trial method**

### **11.1. Overview**

Shock patients with cardiogenic shock caused by acute myocardial infarction, myocardial disease, myocarditis, etc. will be registered both retrospectively and prospectively for two and a half years before and after IRB approval. Patients undergoing coronary intervention and treatment are performed according to the standard method recommended by the Korean Society of Cardiology. If the patient satisfies the above conditions and meets other inclusion and exclusion criteria, we obtain the patient's consent and enroll them in the study. On the day of shock occurrence, we perform physical measurements, blood tests, investigate the medication being taken, and record the most severe signs of vitality on that day. The maximum dose of medication used for shock treatment, the insertion of a left ventricular assist device, and indicators of shock deterioration and improvement are followed up. We conduct tests scheduled for the day of shock occurrence and one month, six months, and twelve months afterward to confirm whether a death event occurred. If the subject is unable to visit the hospital due to unavoidable circumstances, the trial responsible person or the person delegated by the trial responsible person may follow-up and check the subject's survival status and death event by phone.

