## 12. Observation items/clinical examination items and observation/testing methods

### 12.1. Visit 1 (day of shock occurrence)

#### ① Written informed consent for patients enrolled

According to the scope of data collection, it is divided into prospective data collection subjects and retrospective data collection subjects.

- Prospective data collection subjects: The day of shock occurrence is after the IRB approval date
- Retrospective data collection subjects: The day of shock occurrence is before the IRB approval date

For prospective data collection subjects, before entering the clinical trial, the purpose and content of the trial should be explained in detail to the subject or legal guardian (in the case of a subject who cannot provide consent for the trial), and the written consent form should accurately record the signature dates of the subject and investigator. The original signed consent form is kept by the subject, and a copy is provided to the subject. If the subject is unable to consent on the day of the shock occurrence, the consent form is obtained from the representative of the accompanying subject. In this case, the principal investigator and sub-investigator must inform the subject or the subject's representative about the clinical trial as soon as possible and obtain consent to continue participating in the trial. If the subject recovers to a condition where consent can be given, the consent form is obtained from the subject.

For retrospective data collection subjects, only data corresponding to the study protocol are collected until IRB approval is obtained without written consent. However, among shock occurrence subjects before IRB approval, those who have obtained written consent are eligible for both prospective and retrospective data collection.

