## **15. Evaluation criteria for effectiveness, and evaluation and interpretation methods (statistical analysis)**

### **15.1. Primary Endpoint**

In-hospital death

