### **20.2. Informed consent form**

Patients who have heard sufficient explanation about the study and have voluntarily written the informed consent form are eligible to participate in the clinical trial. If there are any changes regarding safety during the study, signatures must be obtained from all participants for the proposed modifications. Researchers must inform patients that they have the right to refuse participation freely and may withdraw from the study at any time without any future disadvantage to their treatment. If the patient is deemed to have understood the research participation sufficiently, the patient can sign the informed consent form. The researcher provides the patient with a copy of the signed informed consent form.

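### Four clauses make consent a condition of entry for everyone, but section 12.1 collects pre-approval patients without it; no rule says which governs, and the consent reading would under-represent in-hospital deaths

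*Protocol*

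**What the plan says.** Consent as a condition of entry, with no retrospective exception:

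- Section 9.1, criterion 5 (repeated in the Summary): "Those voluntarily consenting to the medical records and the data necessary for the study during the entire study period". It mentions neither a signature nor a guardian.
- Clinical trial flow chart, footnote 1: "There must be a signature from the patient or their legal guardian on the consent form". The footnote then refers to the retrospective part by name: "As this study is a retrospective and prospective registry study, data can be collected from patients who meet the selection criteria", and makes this depend on consent to record access.
- Section 11.1, which describes registration both before and after IRB approval: "we obtain the patient's consent and enroll them in the study".
- Section 20.2: patients who "have voluntarily written the informed consent form are eligible to participate in the clinical trial". It mentions no guardian.

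Consent not required for pre-approval patients:

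- Section 12.1 separates subjects by whether shock occurred before or after IRB approval. For the earlier group, "only data corresponding to the study protocol are collected until IRB approval is obtained without written consent". It adds that among these patients "those who have obtained written consent are eligible for both prospective and retrospective data collection".

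The primary endpoint in section 15.1 is "In-hospital death". Section 15.3 expects it in about 40% of patients, or roughly 400 deaths.

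**The concern.** The two sets of clauses give opposite answers to one question: may a patient who had shock before IRB approval, and from whom no consent was obtained, enter the cohort? Section 9.3 expects ten hospitals to take part, and each has to choose.

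The choice matters because consent sought after the event depends on the endpoint. A survivor can be asked. A patient who died in hospital can enter only through a guardian under footnote 1, and not at all on a literal reading of criterion 5 or section 20.2. Unless families of the deceased consent as often as survivors do, in-hospital mortality is underestimated. The logistic model of in-hospital death and the device comparison in section 15.3 use the same selected patients. Deaths that never entered the cohort cannot be restored by analysis.

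**Working it through.** **Inputs from the protocol.** N = 1,000, with 400 device and 600 no-device patients (9.3). Expected mortality is 40% (15.3). The planning rates are 0.3 and 0.4 (9.3).

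**Assumptions, because the protocol gives no figure.** The retrospective share f is taken as 50%, from the equal two-and-a-half-year windows before and after approval in section 11.1, and varied from 30% to 70%. The consent rate among retrospective survivors is c, the consent rate among families of the deceased is g, and alpha is 0.05 two-sided.

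**The protocol's own figures.** Deaths: 0.40 × 1,000 = 400. Power for 0.3 v 0.4 with 400 and 600 patients, using the continuity correction the protocol cites, is 88.9% (stated: about 88%). With 360 and 540 it is 85.3% (stated: 84%). Both are close enough to serve as a baseline.

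**Observed mortality if the consent rule is applied to pre-approval patients.**

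Retrospective half: 0.4g / (0.4g + 0.6c). With c = 0.8, 300 × 0.8 = 240 of its survivors and 200g of its deaths are kept. The prospective half contributes 500 patients and 200 deaths.

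| g | Retrospective mortality | Pooled mortality |
|---|---|---|
| 0 | 0% | 200/740 = 27.0% |
| 0.2 | 0.08/0.56 = 14.3% | 240/780 = 30.8% |
| 0.5 | 0.20/0.68 = 29.4% | 300/840 = 35.7% |
| 0.8 | 0.32/0.80 = 40% | 360/900 = 40% |

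The last row has g = c, and there is no bias.

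**Sensitivity to the retrospective share.** Take the extreme case g = 0, with all survivors consenting. Pooled mortality is 0.4(1 − f) / [0.4(1 − f) + 0.6]:

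- f = 30%: 280/880 = 31.8%
- f = 50%: 200/800 = 25.0%
- f = 70%: 120/720 = 16.7%

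**Device comparison, same loss in both groups** (f = 50%, g = 0, c = 1). Device: 60 deaths in 60 + 280 = 340, or 0.176. No device: 120 deaths in 120 + 360 = 480, or 0.250. The odds ratio is (0.250/0.750)/(0.176/0.824) = 1.56, unchanged from the planning value, but the risk difference shrinks from 0.10 to 0.074. Continuity-corrected power falls from 88.9% to 68% (80% at f = 30%, 48% at f = 70%).

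**Device comparison, unequal loss.** Let true mortality be 40% in both groups, f = 50%, c = 1, with g = 0.5 in the device group and 0 in the other. Device: (0.2 + 0.1)/(0.3 + 0.6) = 0.333. No device: 0.2/(0.2 + 0.6) = 0.250. The odds ratio is 0.500/0.333 = 1.5 where none exists. With the two values of g exchanged it is 0.67.

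So equal loss lowers absolute risks and power, while loss that differs by group also distorts the odds ratio. The same holds for any predictor in the logistic model.

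**The case against.** The strongest reply is that section 12.1 is the only place that defines retrospective and prospective subjects and gives each its own consent rule. A specific rule normally overrides general wording, and the Summary has pre-approval cases verified from medical records from January 2014. If every centre reads it that way, consent does not select on in-hospital death and the primary endpoint is sound. This stands as a limit on the consequence. It does not remove the conflict, because footnote 1 also speaks about the retrospective part and asks for consent there, and nothing ranks the two.

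A reader might infer three stronger things that the documents do not support.

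- *That all these clauses demand a signature.* Criterion 5 speaks only of consenting. The signature comes from footnote 1 and the written form from section 20.2.
- *That the consent rule removes the dead from the retrospective cohort.* Footnote 1 accepts a legal guardian's signature, so the loss may be partial, and there is none if families consent as often as survivors.
- *That mortality in about half the cohort will be underestimated.* This happens only where a centre sets 12.1 aside. The retrospective share is not stated, and the consent rates above are hypothetical.

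It might also be objected that the lack of a censoring or delayed-entry rule for retrospective subjects who consent later is no fault of a protocol. That is right: such detail can sit in the SAP, and it is raised below only as a secondary point.

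**Conclusion.** The contradiction is in the current text, and it bears on who may enter the cohort. If a centre applies the consent rule to pre-approval patients, in-hospital deaths are under-represented relative to survivors unless families consent equally often. Mortality is then underestimated, and the predictor model and device comparison are affected as shown. If 12.1 is followed everywhere, this bias does not arise.

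Under the stated assumptions (half retrospective, 80% of survivors consenting, true mortality 40%) pooled mortality lies between 27% and 40%, depending on how often families consent. That is an illustration of scale and not a forecast. Because the protocol already contains a rule that avoids the bias, this is a should-fix point: a cheap clarification that protects the primary endpoint.

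**What to change.** - Reconcile the Summary, section 9.1 criterion 5, flow-chart footnote 1, section 11.1 and section 20.2 with section 12.1, by limiting the consent requirement to prospective subjects and to post-approval follow-up. All five places need the edit; changing only some would leave the contradiction.
- State in section 12.1 that, within the waiver described there and as confirmed by the IRB, all eligible pre-approval patients are entered from records regardless of survival. The scope of the waiver is for the IRB to settle; the protocol does not show what was approved.
- Report in-hospital mortality separately for the retrospective and prospective cohorts, so that any selection is visible.
- Secondary, for the SAP: post-approval follow-up of pre-approval patients exists only for those who consent. Follow-up survival analyses should censor non-consenters at IRB approval and should not count the time before consent that consenters had to survive, for example by delayed entry at the consent date.

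The cost is wording in six places, IRB approval of the amendment (which section 20.1 requires anyway), one split table and a small change to the survival model. No new data items are needed.
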